**Exclusion Criteria:**

- Parents with psychiatric disorders.
- Children with neurodevelopmental disorders.
- Children with physical health issues requiring regular medication or frequent medical visits.

**Termination Criteria:**

- When participants wish to withdraw from the study.

## 8.4 Population Size

- **Sample Size:**

This quasi-experimental study aims to compare the means before and after the experiment. Since no prior study is available, there's no reference data for calculating the sample size. The sample size is estimated using G power software version 3.1.9.7, specifying a statistical test as paired t-tests and a power analysis as A priori: Compute required sample size. A significance level  $\alpha=0.05$ , a test power of 0.9 (90%), and an effect size  $d=0.5$  (medium) were used for calculations. The estimated sample size was at least 44 participants. To compensate for potential loss of participants due to follow-up issues or incomplete data (20% attrition), the final sample size is set at 55 participants.

## 8.5 Variables

**Independent Variables:**

- **Parental Factors:** Age, gender, education, occupation, income, marital status, household size, number of children, time spent with children.
- **Child Factors:** Age, gender, temperament.
- **Activity:** Sustained shared thinking-based activity.

**Dependent Variables:**

- **Parental Empowerment.**
- **Perception of children's development.**

## 8.6 Variable Definitions

- **Sustained Shared Thinking-Based Activity:** Activities conducted between parents and children that involve brainstorming and idea exchange to generate cognitive outcomes, with tools created by the research team as mediators.

- **Parental Empowerment:** The psychological process and outcomes where parents feel capable of managing and handling parenting roles effectively.
- **Perception of Children's Development:** Parents' recognition of their child's progress in thinking, reasoning, and language skills.

### 8.7 Informed Consent and Recruitment Process

- The study will be advertised through communities. Additionally, announcements will be made in schools with kindergarten levels. Interested participants can contact the research team via telephone and chat application.
- Those interested can scan the QR code and fill in initial information based on inclusion and exclusion criteria. If eligible, the research team will contact the potential participants.
- The researcher will provide information about the study and obtain consent directly from participants, providing research information sheets and consent forms. Verification of participants will be done by taking a photo with their child and sending it to the research team.

### 8.8 Research Methodology

1. Obtain research approval from the Ethics Review Committee of the Faculty of Medicine Vajira Hospital, Navamindradhiraj University.
2. Develop questionnaires on parental empowerment and perception of children's cognitive development.
3. Conduct a review by experts.
4. Assess reliability and validity.
5. Develop sustained shared thinking activities for the research.
6. Advertise the study through community leaders and contact schools with kindergarten levels to reach more parents.
7. Select participants according to the inclusion and exclusion criteria.
8. Provide research information and request consent via Line (consent will be obtained by filling out the name and pressing the consent button in a Google form). Participants' identities will also be verified by sending a photo with their child to the research team.
9. Collect baseline data, including general information and questionnaires on parental empowerment (15 minutes to complete via Google form on Line or phone interview if necessary).
10. Explain the activity details that parents need to conduct with their children for 6 weeks. Tools and manuals created by the research team will be provided. Activities will be sent weekly, requiring at least one 25-30 minute session per week. Parents must send photos of completed tasks and reflection questions weekly.
11. Collect data after the 3rd and 6th (final) activity sessions, and three months after the final session using questionnaires on parental empowerment and children's cognitive development, as well as open-ended questions about their experience (15-20 minutes to complete).
12. Verify completeness of questionnaires and analyze the data statistically.

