## 8.11 Data Analysis

- Descriptive Statistics: Utilizing basic statistics, including percentage, mean, and standard deviation.
- Comparison Analysis: Analyzing parental empowerment scores and perception of children's cognitive development scores before the activities, after the 3rd and 6th sessions, and 3 months post-activities using ANOVA and Linear Mixed Effect Model.
- Qualitative Analysis: The team responsible for designing the exercises will not be involved in data analysis.

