## 8.12 Dummy table

| Parent's information      | n | percentage |
|---------------------------|---|------------|
| Age                       |   |            |
| Sex                       |   |            |
| Education                 |   |            |
| Occupation                |   |            |
| Income                    |   |            |
| Marital status            |   |            |
| Family type               |   |            |
| Number of children        |   |            |
| Time spent with the child |   |            |

| Child's information | n | percentage |
|---------------------|---|------------|
| Age                 |   |            |
| Sex                 |   |            |
| Character           |   |            |

| Pre-test Questionnaire | Score | SD | Level |
|------------------------|-------|----|-------|
| parental empowerment   |       |    |       |
| cognitive development  |       |    |       |
| literacy skill         |       |    |       |

| Post-test Questionnaire | Score  |        |          | SD     |        |          |
|-------------------------|--------|--------|----------|--------|--------|----------|
|                         | Week 3 | Week 6 | 3 months | Week 3 | Week 6 | 3 months |
| parental empowerment    |        |        |          |        |        |          |
| cognitive development   |        |        |          |        |        |          |
| literacy skill          |        |        |          |        |        |          |

| Variables             | Pre-test (SD) | Post-test (SD) | t | p-value |
|-----------------------|---------------|----------------|---|---------|
| parental empowerment  |               |                |   |         |
| cognitive development |               |                |   |         |
| literacy skill        |               |                |   |         |

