## 13. Potential Challenges and Solutions

This research is conducted at home by the parents themselves, requiring cooperation and honesty from the participants, as it demands a considerable amount of time and effort. Therefore, there may be challenges regarding cooperation. The research team will address this by periodically checking in, providing guidance, and keeping communication channels open for participants to reach out. Additionally, at the end of each activity booklet, there will be reflective questions for parents to complete, and they are required to send photos of these reflections to the research team each week after completing the activities.

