## **16. Compensation for Volunteers (Travel/Time Compensation)**

Each participant will receive a total compensation of 1,800 Baht for participating in the research, with 300 Baht given after each activity session.

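### Post-tests are tied to the 3rd and 6th sessions in the methods but labelled by week in the tables, and no assessment time is defined for parents who stop early

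*Protocol*

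**What the plan says.** Section 8.8 of the protocol sets the collection times in step 11: "Collect data after the 3rd and 6th (final) activity sessions, and three months after the final session". Section 8.11 compares scores "before the activities, after the 3rd and 6th sessions, and 3 months post-activities using ANOVA and Linear Mixed Effect Model", which again uses sessions for the first two post-tests. The post-test table in section 8.12 heads the same columns "Week 3 | Week 6 | 3 months".

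The delivery schedule is in step 10 of section 8.8: "Explain the activity details that parents need to conduct with their children for 6 weeks", and "Activities will be sent weekly, requiring at least one 25-30 minute session per week". Section 16 pays a total of 1,800 Baht, "with 300 Baht given after each activity session", which implies six paid sessions.

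The only termination criterion in section 8.3 is "When participants wish to withdraw from the study". Section 13 notes that the study asks a lot of parents and adds: "Therefore, there may be challenges regarding cooperation". Its response is check-ins, guidance, open contact channels and weekly photos of the reflections.

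**The concern.** The two ways of fixing the assessment times are interchangeable only if every parent keeps exactly to one session a week. The protocol itself foresees that some will not.

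Two things follow when a parent departs from that pace. First, a parent who stops before the sixth session but does not withdraw is still in the study under section 8.3, yet step 11 gives no date for the second post-test. The three-month date is also unclear, because step 11 equates the final session with the sixth. Second, a parent who falls behind is measured later than the column heading under which the score is tabulated.

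Whether and when an outcome is collected can therefore depend on adherence to the activity under test. The study compares means before and after (section 8.4) and describes no control group, so nothing offsets a selection of parents who kept going. If those who stop tend to benefit less, the observed change at the sixth session and at three months is too large. An analysis plan can say how missing scores are handled, but it cannot recover questionnaires that were never sent.

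**Working it through.** **1. The plan's own figures.** Section 8.4 gives a paired t-test, alpha 0.05, power 0.90, d = 0.5 and 20% attrition. Sidedness is not stated. With the noncentral t distribution (n − 1 degrees of freedom, noncentrality d√n), a two-sided test first reaches the target at n = 44, with power 0.9000. Inflation gives 44 / (1 − 0.20) = 55. Both stated figures reproduce, and neither depends on the timing rule.

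**2. Session count against week labels.** 1,800 / 300 = 6 paid sessions over a 6-week programme. At one session a week, session 3 falls in week 3 and session 6 in week 6. Applying step 11 literally to other patterns gives:

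| Parent's pattern | 3rd-session post-test | 6th-session post-test | Three-month post-test |
|---|---|---|---|
| Exactly one session each week | Week 3 | Week 6 | Clear date |
| Finishes behind schedule | On time or late | After week 6 | Late |
| Stops after session 3, 4 or 5, does not withdraw | Collected | Not defined | No clear date |
| Stops before session 3, does not withdraw | Not defined | Not defined | No clear date |
| More than one session in some weeks | Possibly before week 3 | Possibly before week 6 | Possibly early |

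The last row is possible because one session a week is a minimum with no stated maximum. Only the first row fits both the methods text and the table labels.

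**3. Possible size of the selection effect (illustration).** These inputs are assumptions: a share f of parents stops early and is not assessed at the later times; completers gain 0.5 SD (the value of d in section 8.4); stoppers gain e.

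Mean over all parents = (1 − f) × 0.5 + f × e. Overstatement = 0.5 / that mean − 1.

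- f = 20%, e = 0: 0.8 × 0.5 + 0.2 × 0 = 0.40; 0.50 / 0.40 = 1.25, or 25%.
- f = 20%, e = 0.25: 0.8 × 0.5 + 0.2 × 0.25 = 0.45; 0.50 / 0.45 = 1.11, or 11%.
- f = 30%, e = 0: 0.7 × 0.5 = 0.35; 0.50 / 0.35 = 1.43, or 43%.
- f = 30%, e = 0.25: 0.7 × 0.5 + 0.3 × 0.25 = 0.425; 0.50 / 0.425 = 1.18, or 18%.
- Any f, e = 0.5: no overstatement.

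**4. Power if everyone is assessed.** Assume a within-group SD of change of 1 and all 55 measured. The overall SD is √(1 + f(1 − f)(0.5 − e)²). For f = 20% and e = 0 this is √1.04 = 1.02, so d = 0.40 / 1.02 = 0.392 and power is 0.82. With e = 0.25, d = 0.448 and power is 0.90. For f = 30%, d = 0.341 with power 0.70 at e = 0, and d = 0.422 with power 0.87 at e = 0.25. For comparison, 44 completers (80% of 55) with d = 0.5 have power 0.90.

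**The case against.** The strongest reply is that the protocol describes one schedule in two vocabularies. Activities go out weekly for six weeks, at least one session a week is required, and six sessions are paid. By design, session 3 belongs to week 3 and session 6 to week 6. This stands for parents on schedule, so it would be wrong to infer that the assessments have no calendar anchor. It does not settle what happens to the others.

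A reader might also infer that parents who skip or stop have no post-test at all. The document does not support that. A parent who stops after session 4 already has the third-session score, and one who finishes late is measured late, not lost. Only a parent who stops before session 3 has no defined post-test on a literal reading. Nothing says that such parents go unassessed, and missing sessions does not end participation.

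Nor does any section restrict the analysis to completers. Section 8.11 names a linear mixed model, which can use partial follow-up. It also names ANOVA, and the pre/post t table in section 8.12 needs complete pairs, but neither amounts to a completer population. Analysis sets and missing-data handling may sit in a statistical analysis plan that is not shown, and their absence is no part of this point. What remains is that a mixed model does not remove bias if missingness depends on the unobserved gain.

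Finally, the 20% in section 8.4 covers loss to follow-up and incomplete data, not failure to reach session 6, and some of those losses would occur under any timing rule. The figure is only a borrowed scale here. Zero gain in every stopper is an extreme assumption, given that some will have done four or five sessions. The contacts in section 13 could be used to reach parents who fall behind, but the section does not say that they secure a questionnaire from a parent who has stopped.

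**Conclusion.** The point holds in limited form. Sections 8.8 and 8.11 anchor the first two post-tests to sessions and section 8.12 labels them by week, and the two coincide only at exactly one session a week. For parents who stop before the sixth session without withdrawing, the sixth-session assessment is undefined and the three-month date unclear. Those who fall behind are measured late under a fixed week label.

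The consequence is a risk to the later before-after estimates, chiefly at the sixth session and three months, that they over-represent adherent parents. An upward direction is plausible because parents who gain less may be likelier to stop, but the document gives no evidence of this. With 20% stopping and completers gaining 0.5 SD, the overstatement is 25% if stoppers gain nothing, 11% if they gain 0.25 SD, and nil if they gain as much as completers. These figures rest on assumed inputs and do not measure a bias in the trial. The sample size of 55 is not affected by the timing rule. The wording should be corrected before data collection, since the loss cannot be repaired later.

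**What to change.** Amend step 11 of section 8.8, and align sections 8.11 and 8.12 with it, along these lines:

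*All enrolled parents are sent the questionnaires at week 3, at week 6 and 3 months after week 6, counted from the date the first activity is sent, regardless of how many sessions they have completed, unless they withdraw from the study. The number of sessions completed by each assessment is recorded.*

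This keeps the nominal schedule for parents on pace and gives every other parent a defined date.

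The cost is a sentence in the protocol, matching labels in two sections, and extra reminders to non-adherent parents over the existing Line channel. The estimated effect may be smaller than among completers, and power may fall with it: under the assumptions above, to 0.82 at 20% stopping with no gain in stoppers and 0.70 at 30%, or 0.90 and 0.87 if stoppers gain 0.25 SD.

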## 8.9 Measurement

1. Questionnaire on general information of participants, covering parents' details (age, gender, education, occupation, income, marital status, household members, number of children, time spent with children) and children's details (age, gender, character).
2. Parental Empowerment Questionnaire.
3. Perception of Children's Cognitive Development Questionnaire.
4. Questionnaire on experience after participating in the study activities.

## 8.10 Data Collection

Data collection will be carried out by having eligible participants complete questionnaires and assessments. Data will be recorded individually, without displaying any names or information that could identify the participants. Only the research team will have access to this data set, and the team that designed the exercises will not be involved in selecting participants.

Collected data will be checked for completeness, scored according to established criteria, and prepared for statistical analysis.

## 8.11 Data Analysis

- Descriptive Statistics: Utilizing basic statistics, including percentage, mean, and standard deviation.
- Comparison Analysis: Analyzing parental empowerment scores and perception of children's cognitive development scores before the activities, after the 3rd and 6th sessions, and 3 months post-activities using ANOVA and Linear Mixed Effect Model.
- Qualitative Analysis: The team responsible for designing the exercises will not be involved in data analysis.

## 8.12 Dummy table

| Parent's information      | n | percentage |
|---------------------------|---|------------|
| Age                       |   |            |
| Sex                       |   |            |
| Education                 |   |            |
| Occupation                |   |            |
| Income                    |   |            |
| Marital status            |   |            |
| Family type               |   |            |
| Number of children        |   |            |
| Time spent with the child |   |            |

| Child's information | n | percentage |
|---------------------|---|------------|
| Age                 |   |            |
| Sex                 |   |            |
| Character           |   |            |

| Pre-test Questionnaire | Score | SD | Level |
|------------------------|-------|----|-------|
| parental empowerment   |       |    |       |
| cognitive development  |       |    |       |
| literacy skill         |       |    |       |

| Post-test Questionnaire | Score  |        |          | SD     |        |          |
|-------------------------|--------|--------|----------|--------|--------|----------|
|                         | Week 3 | Week 6 | 3 months | Week 3 | Week 6 | 3 months |
| parental empowerment    |        |        |          |        |        |          |
| cognitive development   |        |        |          |        |        |          |
| literacy skill          |        |        |          |        |        |          |

| Variables             | Pre-test (SD) | Post-test (SD) | t | p-value |
|-----------------------|---------------|----------------|---|---------|
| parental empowerment  |               |                |   |         |
| cognitive development |               |                |   |         |
| literacy skill        |               |                |   |         |

## 9. Risks and Possible Side Effects

There is a potential psychological risk because participating in activities with children requires physical and emotional effort, along with answering some of the questions may negatively impact mental health. Therefore, participants have the right to refrain from answering or to stop answering the questionnaire, and they can also withdraw from the research. If severe psychological impacts occur, the research team will recommend counseling services with a psychologist or psychiatrist from the Faculty of Medicine at Vajira Hospital.

## 10. Expected Benefits and Impacts

- The effectiveness of sustained shared thinking activities in empowering parents.
- Development of a questionnaire to measure parental empowerment.
- 

## 11. Ethical Considerations

This research follows the fundamental ethical principles of the Belmont Report:

1. **Respect for Persons:** Providing complete information about the research project to participants without concealing any details. All participants voluntarily agree to participate. Documents related to the research will be kept confidential and accessible only to those involved in the research. Data will be presented in an aggregate form without mentioning the real names of the participants. The research must be approved by an ethics committee before commencing, and all participants or their legal representatives must sign a consent form.
2. **Beneficence:** Participants will be informed of the risks and benefits associated with participating in the research. Participants will also receive guidance on what to do if any abnormalities are detected.
3. **Justice:** Even if individuals do not wish to participate in this research, they will still receive full medical care according to standard treatment guidelines.
- 4.

## 12. Research Limitations

Access to research participants will be conducted remotely, primarily through the Line application. This may pose limitations for those who are not familiar with using this type of technology.

## 13. Potential Challenges and Solutions

This research is conducted at home by the parents themselves, requiring cooperation and honesty from the participants, as it demands a considerable amount of time and effort. Therefore, there may be challenges regarding cooperation. The research team will address this by periodically checking in, providing guidance, and keeping communication channels open for participants to reach out. Additionally, at the end of each activity booklet, there will be reflective questions for parents to complete, and they are required to send photos of these reflections to the research team each week after completing the activities.

#### 14. Research Management and Study Timeline

| Step | Details                                          | Month |   |   |   |   |   |   |   |   |    |    |    | Output                                                               |
|------|--------------------------------------------------|-------|---|---|---|---|---|---|---|---|----|----|----|----------------------------------------------------------------------|
|      |                                                  | 1     | 2 | 3 | 4 | 5 | 6 | 7 | 8 | 9 | 10 | 11 | 12 |                                                                      |
| 1    | Scope problems and objectives                    | ●     |   |   |   |   |   |   |   |   |    |    |    |                                                                      |
| 2    | Literature review and drafting research proposal | ●     |   |   |   |   |   |   |   |   |    |    |    |                                                                      |
| 3    | Submission for ethical review                    |       | ● | ● |   |   |   |   |   |   |    |    |    |                                                                      |
| 4    | Develop questionnaire and intervention tools     |       |   |   | ● |   |   |   |   |   |    |    |    | Empowerment questionnaire and sustained-shared thinking intervention |
| 5    | Collaboration and planning                       |       |   |   | ● | ● |   |   |   |   |    |    |    |                                                                      |
| 6    | Pre-test data collection                         |       |   |   |   | ● | ● | ● |   |   |    |    |    |                                                                      |
| 7    | Participants conducting experimental activities  |       |   |   |   | ● | ● | ● | ● | ● |    |    |    |                                                                      |
| 8    | Post-test data collection                        |       |   |   |   |   |   |   | ● | ● | ●  |    |    |                                                                      |
| 9    | Data compilation                                 |       |   |   |   |   |   |   |   |   | ●  | ●  |    |                                                                      |
| 10   | Analyze and Interpret the Research Results       |       |   |   |   |   |   |   |   |   |    | ●  | ●  |                                                                      |
| 11   | Disseminate Research Findings                    |       |   |   |   |   |   |   |   |   |    |    | ●  | Full manuscript                                                      |

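### The project timeline closes post-test collection at the end of month 10, before the 3-month assessment falls due for any parent who starts in month 7

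*Protocol*

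**What the plan says.** Protocol section 8.8, step 10, sets the length and pace of the programme: "Explain the activity details that parents need to conduct with their children for 6 weeks", and "Activities will be sent weekly, requiring at least one 25-30 minute session per week". Step 11 sets the outcome assessments: "Collect data after the 3rd and 6th (final) activity sessions, and three months after the final session".

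The dummy tables in section 8.12 place week 3, week 6 and 3 months together under one post-test heading.

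The timeline in section 14 draws these rows:

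| Row | Step | Months marked |
|---|---|---|
| 6 | Pre-test | 5-7 |
| 7 | "Participants conducting experimental activities" | 5-9 |
| 8 | "Post-test data collection" | 8-10 |
| 9 | Compilation | 10-11 |
| 10 | Analysis | 11-12 |
| 11 | Dissemination | 12 |

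**The concern.** Row 8 is row 6 shifted by exactly three months. Step 11, however, counts three months from the last session, and that session comes more than a month after the first. The row therefore appears to omit the length of the programme. It also opens after the earliest parents should have completed both in-programme assessments.

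The 3-month score is the only measurement taken after the activities have stopped, so it is the only evidence on whether an effect lasts. If staff work to the chart, parents who enrol late either have no 3-month score or have one taken early and tabulated as 3 months. Whether a score is missing or mistimed would then depend on enrolment date. An analysis plan cannot repair data that were not collected, or not collected when intended.

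**Working it through.** **Convention.** Month k is the interval from k-1 to k in elapsed months, and a month is 30.44 days. Row 6 then covers 4.0 to 7.0, row 7 covers 4.0 to 9.0, and row 8 covers 7.0 to 10.0.

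**The plan's own sample size.** Section 8.4 uses a paired t-test with d = 0.5, alpha 0.05 and power 0.90. Sidedness is not stated. The two-sided noncentral-t calculation gives n = 44 (power 0.900), and 44 / (1 - 0.20) = 55, as printed. The one-sided version gives 36. The figure reproduces; the timeline point does not rest on it.

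**Interval from first activity to the 3-month assessment.**
- Six full weeks: 42 / 30.44 = 1.38 months; 1.38 + 3 = 4.38.
- Five weeks from first to sixth weekly session: 35 / 30.44 = 1.15 months; 1.15 + 3 = 4.15.

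**Result that needs no enrolment assumption.**
- A parent starting on the first day of month 7 (time 6.0) is due at 6.0 + 4.38 = 10.38, or 6.0 + 4.15 = 10.15. Both are past 10.0, so every month-7 starter is late.
- The latest start that is still on time is 10 - 4.38 = 5.62, or 10 - 4.15 = 5.85. Some parents starting in the later part of month 6 are therefore late too.
- A final session in month 9 (8.0 to 9.0) puts the assessment at 11.0 to 12.0, which is month 12. Row 7 plans for this, and it follows from row 6 without any delay: 7.0 + 1.38 = 8.38. By then collection and compilation have ended, and analysis and dissemination are under way.

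**Share late (the enrolment pattern is an assumption).** For starts uniform from 4.0 to an upper limit U, the share late is (U - latest on-time start) / (U - 4).

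| Variant | Calculation | Share late | Of 55 |
|---|---|---|---|
| Six weeks, U = 7 | (7 - 5.62) / 3 | 46% | about 25 |
| Six weeks, U = 7.25 (starts run about a week over) | (7.25 - 5.62) / 3.25 | 50% | about 28 |
| Six weeks, U = 9 - 1.38 = 7.62 (starts until row 7 just allows completion) | (7.62 - 5.62) / 3.62 | 55% | about 30 |
| Five weeks, U = 7 | (7 - 5.85) / 3 | 38% | about 21 |
| All start by 5.62 | none beyond the limit | 0% | 0 |

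**By start month** (six-week count, uniform within the month; week 3 is at 21 / 30.44 = 0.69 months):

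| Start month | 3-month assessment due | Due after row 8 closes | Week 3 due before row 8 opens | Week 6 due before row 8 opens |
|---|---|---|---|---|
| 5 | 8.38 to 9.38 | 0% | 100% | 100% |
| 6 | 9.38 to 10.38 | 38% | 100% | 62% |
| 7 | 10.38 to 11.38 | 100% | 31% | 0% |

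Over all uniform starts, week 3 falls before the row opens for (7 - 0.69 - 4) / 3 = 77%, and week 6 for (7 - 1.38 - 4) / 3 = 54%.

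**The case against.** The best defence is that section 14 is a month-level management chart and that section 8.8 is the operative schedule. Section 8.8 states the 3-month timing plainly, data come by remote questionnaire, and nothing in the chart tells staff to skip an assessment or bring it forward. That stands as a limit on the consequence: data are lost or mistimed only if the chart is followed. It does not remove the contradiction, because the two sections cannot both be carried out for a month-7 starter.

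Row 8 might also be read as the 3-month assessment alone. That would dispose of the early-opening problem but not the late one, and the shared post-test heading in section 8.12 speaks against it.

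Three stronger readings are tempting and are not supported.
- **That about half of the follow-ups will be lost.** The 46% needs uniform enrolment, which the protocol does not state, and being due late is not the same as being lost.
- **That all week-3 and week-6 assessments precede the row.** No month-7 starter's week-6 assessment does.
- **That power falls to a definite lower figure.** A reader could take 54% of 55 (about 30), remove 20% (about 24) and obtain about 65% for a paired test at d = 0.5. This assumes that every late assessment is lost and that only complete baseline-to-3-month pairs are analysed. Section 8.4 does not tie its 90% to that contrast, and section 8.11 plans a mixed model, which keeps parents without a 3-month score. The baseline-to-week-6 comparison is not cut off by the month-10 closure: the last week-6 assessment is due at 8.38, or 9.0 if activities run to the end of row 7.

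**Conclusion.** The point holds: the timeline as drawn cannot deliver the protocol's own assessment schedule. It is certain for every month-7 starter under either way of counting the programme, and it extends to some later month-6 starters. Beyond that, the size depends on enrolment: about 46% under uniform starts over months 5-7, 38-55% across the variants with starts spread over at least that window, none if all start by about mid-month 6, and all if everyone starts in month 7. At the other end, the row opens too late for month-5 starters and many month-6 starters.

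What is at risk is the completeness and timing of the 3-month score, in a pattern tied to enrolment date. No particular loss of power should be claimed.

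**What to change.** Reconcile sections 8.8 and 14 by one of two routes.

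1. **Extend.** Redraw rows 8-11. Post-test collection runs from month 5 (the first week-3 assessment is due at 4.0 + 0.69 = 4.69) until three months after the last parent's final session, which is in month 12 as the activities are now drawn. Compilation, analysis and dissemination each move about two months later, to months 12-13, 13-14 and 14.
2. **Keep 12 months.** End activity starts, and so pre-test, by about mid-month 6 (5.62 on the six-week count), so that every 3-month assessment falls by the end of month 10. Row 8 must still open in month 5 to cover the week-3 and week-6 assessments.

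The first route costs about two months. The second cuts the start window from 3 months to about 1.62, so enrolling 55 parents would take about 55 / 1.62 = 34 a month instead of 55 / 3 = 18. Neither needs more participants.
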